Our first aim is to determine the effectiveness and efficacy of 3-month use of MS INFoRm on fatigue impact among persons with MS. Our primary outcome will be measured using the Modified Fatigue Impact Scale (MFIS) [23]. We hypothesize that the MS INFoRm group will show significant reductions in fatigue impact compared to the usual care control group.

### Specific aim 2

Our second aim is to determine whether 3-month use of MS INFoRm results in improvement in secondary outcomes of self- efficacy for managing MS fatigue, self-reported cognitive function, depression, and participation and autonomy. The measures we will use to evaluate these outcomes are the Multiple Sclerosis Self-Efficacy Scale (MSSES) [24], the Perceived Deficits Questionnaire (PDQ) [25], Center for Epidemiologic Studies Depression Scale (CES-D) [26], and Impact on Participation and Autonomy Questionnaire (IPA) [27] respectively. We hypothesize that the MS INFoRm group will show significant improvements in self-efficacy for managing MS fatigue, self-reported cognitive function, participation and autonomy, and significant reductions in depression, compared to the usual care control group.

### Specific aim 3

Our third and final aim is to determine whether any improvements in primary and secondary outcomes are maintained among the MS INFoRm users after 6-months. We hypothesize that the beneficial effects of MS INFoRm will be maintained at 6-month follow-up.

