### Group allocation

Group allocation will be based on a random permutated block design, using computerized random number generation. This design was selected because it ensures a 1:1 allocation ratio between the intervention group and the control group and because it will effectively reduce any risk of a systematic bias that may confound the treatment effect (i.e., people from the same MS clinic enrolling sequentially). The block size, which is fixed, will not be disclosed, to ensure concealment. One hundred people will be allocated to the MS INFoRm group and 100 to the usual care control group.

All eligible participants will be provided with a study identification number and password to access the MS INFoRm website. Using the block randomization process described above, each study ID has been assigned to one of the two groups by two of the study investigators. A password-protected file, and the MS INFoRm administrator website, which includes the group allocation for each Study ID, is only be accessible by two of the study investigators. Upon login, participants in the MS INFoRm intervention group will be directed to the intervention website whereas participants in the usual care control group will be directed to the usual care website. Participants will be provided with access to the website for 3-months from time of baseline assessment. Participants will access the website at their own volition, and not be directed on how often to use it as the nature of the intervention is self-directed, in order to replicate real-world use.

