### MS INFoRm intervention website

A description of the sections, content, and features of the MS INFoRm intervention website is provided in Table 1.

**Table 1 Tab1:** MS INFoRm intervention website content and features

Section	Primary Content and Features
1. Initial login page	- Presents introductory video providing user with orientation to website and overview of MS fatigue
2. Basics of fatigue	- Provides definition of fatigue - Provides facts about MS fatigue including prevalence, association with other disease-related factors, and how MS fatigue is different than regular fatigue - Provides description of primary and secondary fatigue - Includes section on tracking fatigue, including description of the benefits of tracking fatigue, how to track fatigue using a printable form, or on the “Rate your Fatigue” section (described below in section 3) of the website - Provides a link to the introductory video (enables users to review initial login page information)
3. Rate your fatigue	- Allows users to rate fatigue level at each visit (limits to one entry per day) from 0 (lowest fatigue) to 10 (highest fatigue) - Presents all ratings in a line graph that shows date and time, and rating
4. Track your goals	- After initial login page, users are prompted to set at least one fatigue management goal - Users are prompted to enter the following for each goal: (a) What do you want to do? (b) When do you want to start doing it? (c) How often do you want to do it? (d) How will you know that you have achieved this goal? (e) How confident are you that you can achieve this goal? - Users can update the answers to question (e) and are asked to rate the goal completion progress at each subsequent login - Users can have 3 goals active at a time, any goals that become achieved are put in a “Goals History” page - Users are prompted to select up to three fatigue management strategies to use to help them accomplish each goal. Strategies are described and can be selected from Sections 5 and 6 (described below) of the website
5. Influencing factors	Each of the following influencing factors, or contributors to secondary fatigue are provided on separate webpages

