### Usual care website

The usual care website includes links to widely available brochures/ pdfs published by the MS Society of Canada entitled “MS Fatigue” [31] and “Living Well With MS: Managing Fatigue” [32]. These pdfs were chosen as they are resources to which clinicians, including those on the research team, often direct their MS patients. A brief description of the contents of each brochure/ pdf is provided on the website prior to presenting the link. The usual care website was designed to visually resemble the intervention website in order to facilitate blinding. We acknowledge, however, that some participants might be able to recognize that they have been allocated to the usual care control group if they have been previously exposed to the usual care resources.

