### Website usage data

User analytic data will be collected from the website (from both groups) in order to track the number of times the site is accessed, length of each visit, specific pages visited, time spent on each page, which worksheets and links were accessed and how often, and to capture all fatigue ratings and goal data entered. These data will be collected to identify delivery fidelity (did participants access all components of the website) and for descriptive analysis of usage patterns and impact of use on outcomes.

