### Statistical analysis

All data will be analyzed in IBM SPSS Statistics Version 24. Scores on all outcome measures will be calculated according to manual instructions for each measure. Unusually high or low values will be checked against the raw data to confirm accuracy. Descriptive statistics will be calculated for each variable for both the intervention and usual care control group. Score distributions will be checked to ensure that distributional assumptions are met for the hypothesis testing step of the analysis.

The MS INFoRm and usual care groups will be compared on baseline measures and key demographic and disease-related variables that may influence study outcomes (e.g. age, disease duration, education level) to test equivalence of groups. Independent samples t-tests will be used for continuous variables with a normal distribution, Mann Whitney U tests for non-normally distributed data, and chi-square tests for categorical variables. If differences are found, these variables will be used as covariates during hypothesis testing to ensure that group differences at baseline are not responsible for differences in outcomes.

For individuals lost to follow-up, their data will be used in the statistical analysis in the effectiveness analysis as per an intention to treat approach [40]. These individuals will remain in the same group as randomized. The advantage of this approach is that the estimated effect of the intervention will reflect the effect that would actually be achieved in the real world (i.e., effectiveness analysis) when people have differential motivation to use MS INFoRm. Missing data will be imputed using the strategy of last observation carried forward, as this is the most conservative [41].

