Hypothesis 1 states that the MS INFoRm group will show significant reductions in fatigue impact compared to the usual care control group. In order to test hypothesis 1, changes between baseline and 3-month scores on the MFIS will be compared between the MS INFoRm group and the usual care control group using an independent t-test. If the testing for group equivalence indicates that there are baseline differences between the groups at baseline, an analysis of variance with covariates will be used to test hypothesis 1. A *p* < 0.05 will be used as the significance value. In order to test efficacy, or whether MS INFoRm works when delivered as intended, data from only those individuals who have complete baseline and 3-month data and have accessed all of the website content at least once will be used in the analysis. In order to test effectiveness, participants who have missing 3-month scores will be assigned a change score of zero.

Hypothesis 2 states that the MS INFoRm group will show significant improvements in self-efficacy for managing MS fatigue, self-reported cognitive function, participation and autonomy, and significant reductions in depression, compared to the usual care control group. The analysis will use the same approach as hypothesis 1, using zero-value change scores for individuals lost to follow-up. A Bonferroni adjustment will be applied for multiple testing, and therefore the significance value will be set at *p* < 0.0125 (0.05/4 tests).

Hypothesis 3 states that the beneficial effects of MS INFoRm will be maintained at 6-month follow-up. To address this hypothesis, a mixed-effect ANOVA will be used with an unstructured variance-covariance structure, a random intercept and terms for both a linear and quadratic trend. A quadratic trend would be characterized by a sharp improvement immediately post-intervention (3-months), followed by a gradual stabilization of improvement. The five measures (MFIS, MSSES, PDQ, CES-D, and IPA) will be modelled simultaneously and individually. When modelled simultaneously, a significance value of *p* < 0.05 will be used. When modelled individually, a Bonferroni adjustment will be applied for multiple testing, and therefore the significance value will be set at *p* < 0.01 (0.05/5 tests).

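### The efficacy test of Hypothesis 1 selects completers who opened all website content, a post-randomisation filter that asks much more of the MS INFoRm arm than of the control arm

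*Protocol article*

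**What the plan says.** Specific aim 1 is to "determine the effectiveness and efficacy of 3-month use of MS INFoRm on fatigue impact among persons with MS", so efficacy stands beside effectiveness on the primary outcome, the Modified Fatigue Impact Scale (MFIS). It is not labelled supportive or exploratory.

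Under Statistical analysis, Hypothesis 1 is tested with an independent t-test on the change from baseline to 3 months, at p < 0.05, in two ways:

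- Effectiveness: everyone stays in the arm to which they were randomised, and a missing 3-month score becomes a change of zero.
- Efficacy: the purpose is given as "In order to test efficacy, or whether MS INFoRm works when delivered as intended", and the analysis uses "data from only those individuals who have complete baseline and 3-month data and have accessed all of the website content at least once".

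What there is to open differs by arm. Table 1 lists seven sections for MS INFoRm. For the fifth it says "Each of the following influencing factors, or contributors to secondary fatigue are provided on separate webpages", and there are five such factors. Worksheets, diaries, audio examples and the rating and goal tools come on top. For the control arm, "The usual care website includes links to widely available brochures/ pdfs published by the MS Society of Canada"; there are two, each with a short description.

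Use is voluntary (Group allocation): "Participants will access the website at their own volition, and not be directed on how often to use it". Page-level usage is recorded in both arms (Website usage data).

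**The concern.** Membership of the efficacy set depends on what participants do after allocation, and the same words set a different bar in each arm. Getting through the whole MS INFoRm site takes more persistence than opening two brochures. Those retained in the MS INFoRm arm are therefore likely to be a more strongly selected, more motivated group than those retained in the control arm.

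The protocol recognises the selecting variable. It justifies its intention-to-treat analysis by the real-world situation "when people have differential motivation to use MS INFoRm", and the efficacy analysis then selects on that same trait. The only adjustment described is for baseline variables found to differ between the groups. Table 2 contains no measure of motivation, so this adjustment does not deal with the selection.

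At stake is one of the two conclusions promised in Aim 1. If motivated people improve more whichever site they see, the efficacy test can show a benefit from a site that has none. The Dissemination plan ties wider release to the hypotheses being supported, and no rule says which analysis governs if the two disagree.

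**Working it through.** **The plan's own figure.** The total of 200 cannot be reproduced, because the effect size, variances and power are not printed in the article. For orientation only, d = (z_0.975 + z_power) × √(2/n). With 100 per arm and 80% power this gives 0.40; with 66 per arm it gives 0.49.

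**Inputs from the article.** 100 per arm (Group allocation); attrition up to 34% (Sample size), so 100 × (1 − 0.34) = 66 completers per arm; alpha 0.05, taken as two-sided because the article does not say.

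**Assumptions, because the article gives no figures.** q is the share of completers retained in each arm. ρ is the correlation of a latent motivation with MFIS improvement, the same in both arms. There is no treatment effect, and each arm keeps its most motivated share q.

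**Step 1: how different is the bar?** Six undivided sections plus five factor pages make 11 components, against 2 brochures. If each is opened independently with the same probability p, the share opening everything is p^11 against p^2:

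| p | MS INFoRm (11) | Control (2) |
|---|---|---|
| 0.80 | 9% | 64% |
| 0.90 | 31% | 81% |
| 0.95 | 57% | 90% |

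This is an illustration, not a forecast.

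**Step 2: bias with no true effect.** The mean motivation of the top share q is φ(t)/q, with t the cut-off for that share: 0.644 for 60%, 1.159 for 30%, 1.400 for 20% and 0.350 for 80%. Bias in SD units is ρ × (mean in MS INFoRm − mean in control):

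- 60% vs 80%, ρ = 0.1: 0.1 × (0.644 − 0.350) = 0.03
- 30% vs 80%, ρ = 0.3: 0.3 × (1.159 − 0.350) = 0.24
- 20% vs 80%, ρ = 0.5: 0.5 × (1.400 − 0.350) = 0.53

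**Step 3: type I error, 66 completers per arm.** For 30% vs 80% the analysed numbers are 19.8 and 52.8, so SE = √(1/19.8 + 1/52.8) = 0.264. The shift is 0.243/0.264 = 0.92, and the two-sided rejection rate is 0.151. The other rows come from simulation of the t-test (4,000 runs each):

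| Retained, MS INFoRm vs control | ρ | Bias (SD) | Type I error |
|---|---|---|---|
| 80% vs 80% | 0.1 to 0.5 | 0 | 0.046 to 0.050 |
| 60% vs 80% | 0.1 / 0.3 / 0.5 | 0.03 / 0.09 / 0.15 | 0.05 / 0.06 / 0.12 |
| 40% vs 80% | 0.1 / 0.3 / 0.5 | 0.06 / 0.19 / 0.31 | 0.06 / 0.13 / 0.27 |
| 30% vs 80% | 0.3 | 0.24 | 0.15 |
| 20% vs 80% | 0.1 / 0.3 / 0.5 | 0.11 / 0.32 / 0.53 | 0.06 / 0.18 / 0.43 |

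In the last row about 13 and 53 people are left. The equal-retention row confirms that unequal selection drives the bias.

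**Step 4: the other reading of the rule.** If website content means the MS INFoRm site only, controls face no access filter. At 40% vs 100% the bias is 0.10 / 0.29 / 0.48 SD and the type I error 0.08 / 0.24 / 0.57 for the same three correlations. The point holds on either reading.

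**The case against.** The strongest reply is that the as-randomised effectiveness analysis is untouched and that the Discussion frames success around whether the site is effective. Both are true and limit the damage. But Aim 1 also asks for an efficacy conclusion, and a sound effectiveness test does not make the efficacy comparison sound.

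A second reply is that the harm depends on unknown quantities. That stands: at a correlation of 0.1, or at 60% vs 80% retained with a correlation up to 0.3, type I error stays near 5 to 6%. The direction is not certain either. People who improve early may stop browsing while those still fatigued read on, which would work against MS INFoRm.

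Three stronger readings are tempting, and the article does not support them:

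- **That the rule contradicts a self-directed intervention.** The Group allocation section leaves frequency of use to the participant; it does not say that partial coverage is the intended delivery. The Website usage data section equates delivery fidelity with reaching every component, so the efficacy rule agrees with the protocol's own definition.
- **That nearly every control who logs in would qualify.** No retention figure is given. The Usual care website section notes possible earlier exposure to the brochures, and such people may not open them again.
- **That a complier-average analysis must be less precise than the subset.** With 66 per arm the as-randomised SE is √(2/66) = 0.174 SD. Dividing by an uptake of 80% gives about 0.218, below the 0.264 of the 20 vs 53 subset. The two are equal at an uptake of 0.174/0.264, about 66%.

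**Conclusion.** The concern holds in this form: the efficacy test applies a post-randomisation filter whose content is much larger in one arm, so the retained groups are likely to differ in motivation and the comparison has lost the protection of randomisation. The difference in content follows directly from Table 1 and the Usual care website section. The difference in motivation is likely, not documented.

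The size cannot be fixed from the article. Over the assumptions shown, with 66 completers per arm, it runs from negligible (0.03 SD) through 0.24 SD, about half of the 0.49 SD that this number of completers detects with 80% power, to 0.53 SD. The direction favours MS INFoRm only if motivated users improve more in either arm.

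A reader might infer that the trial's main result is compromised. It is not: the finding concerns the efficacy conclusion only.

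**What to change.** 1. Label the all-content completer comparison descriptive or supportive, and state that no efficacy conclusion rests on it.
2. Base the efficacy estimate in Aim 1 on a complier-average causal effect that uses randomisation as the instrument and keeps all randomised participants. In its simplest form this is the as-randomised difference divided by the proportion of the MS INFoRm arm with uptake. Handle missing 3-month scores as in the as-randomised analysis.
3. Define uptake beforehand as any meaningful access to the MS INFoRm site, for example going past the login page, so that those counted as non-users plausibly gain nothing. A higher threshold, such as opening a strategy page, is less safe: the basics, tracking and goal tools in Table 1 could help people who never reach it. The introductory video sits on the login page itself, so the plan should say that seeing it alone is assumed to have no effect.
4. State that use of MS INFoRm by controls through shared logins, which the Discussion says cannot be tracked, is assumed negligible.

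The cost is a little more analysis on usage data already planned. The estimate describes users at the chosen threshold, not people with full exposure. Its standard error is roughly the as-randomised one divided by uptake, so the interval is clearly wider than the as-randomised one when uptake is low. It also inherits the limits of the zero-change rule for missing scores.

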### Sample size

We seek to recruit a total of 200 individuals. The total number of individuals to be recruited is based on calculations of sample size and power for a balanced independent-groups mixed effect model with three time points for our primary outcome (i.e., fatigue impact at baseline, 3 months, 6-months post use). The effect sizes, variances and covariance estimates were obtained from our pilot results [21]. Calculations take into account potential attrition over time, which could be as high as 34% based on our pilot study. This high attrition rate, however, was likely due to limited persistence of research staff for follow-up assessments, which we will attempt to remediate in the proposed project.

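### Giving everyone missing at 3 months a change of zero is not conservative in general: it dilutes the effect under equal loss and can create a false difference in either direction under unequal loss

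*Protocol article*

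**What the plan says.** The Protocol article, under Statistical analysis, keeps participants lost to follow-up in their randomised arm and states a general rule: "Missing data will be imputed using the strategy of last observation carried forward, as this is the most conservative".

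For Hypothesis 1, "changes between baseline and 3-month scores on the MFIS will be compared between the MS INFoRm group and the usual care control group" with an independent t-test at the 0.05 level. For the effectiveness version of that test, "participants who have missing 3-month scores will be assigned a change score of zero". Hypothesis 2 takes the same approach for the four secondary outcomes, "using zero-value change scores for individuals lost to follow-up", at a Bonferroni level of 0.0125. Baseline is the only score before 3 months, so carrying it forward and assigning zero change are one rule.

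Under Group allocation, "One hundred people will be allocated to the MS INFoRm group and 100 to the usual care control group". Under Sample size, the allowance for attrition is a figure "which could be as high as 34% based on our pilot study".

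Zero change is the only handling of missing 3-month scores that the article states for the effectiveness analysis. The efficacy analysis drops incomplete cases but also drops people who did not open all the content, so it does not show what the imputation alone does.

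**The concern.** A missing score is replaced by a constant and then treated as an observation. This has two consequences.

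First, the estimated difference depends on who was reached for interview as well as on what the website did. If both arms improve, zeros pull down the arm that loses more people. If both worsen, zeros flatter that arm. Neither error is conservative by design.

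Second, a block of identical zeros shrinks the standard deviation of change while the sample size still counts as 100 per arm, so the standard error claims more information than was collected.

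At stake is the intention-to-treat result for the primary outcome and all four secondary outcomes, in a trial that allows for substantial attrition. Zero is also hard to defend as the real-world value for a lost participant. The Sample size section puts the pilot's loss down to limited persistence by staff, and a missed interview is not the same as not using the website. Usage is recorded separately in both arms.

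**Working it through.** **Inputs from the article.** 100 per arm; loss of up to 34%, which leaves 100 × (1 − 0.34) = 66 observed per arm; level 0.05, taken as two-sided because sidedness is not stated. The Bonferroni level reproduces: 0.05/4 = 0.0125. The total of 200 cannot be recomputed, because the article does not print the pilot effect size, variances or power; nothing below depends on it.

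**Assumptions.** Change is in units of its own SD (SD = 1), with positive values meaning improvement. Loss by arm ranges from 10% to 34% and the common improvement from 0.3 to 0.8 SD.

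**1. Expected difference.** Let d be the proportion lost, m the mean improvement of those observed, and l the mean improvement that those lost would have shown (T = MS INFoRm, C = control).

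- Zero-filled difference: (1 − dT)mT − (1 − dC)mC
- True difference: the same, plus dT·lT − dC·lC
- Error: dC·lC − dT·lT

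If loss is unrelated to outcome, l = m = μ, and three cases follow:

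- Equal loss: the estimate is (1 − d)(μT − μC), which is 90%, 80% and 66% of the truth at 10%, 20% and 34% loss.
- No change in control: the estimate is (1 − dT)μT, diluted towards zero whatever the imbalance in loss.
- No true effect, common change μ, unequal loss: a false difference of μ(dC − dT).

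**2. Unequal loss, no true effect.** Variance per arm is (1 − d) + d(1 − d)μ². The chance of a significant result favouring MS INFoRm is about P(Z > 1.96 − bias/SE); its nominal value is 2.5%. For μ = 0.5 with 15% and 34% lost:

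- Bias: 0.5 × (0.34 − 0.15) = 0.095
- SE: √((0.882 + 0.716)/100) = 0.126
- Probability: P(Z > 1.96 − 0.75) ≈ 11%

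| Improvement in both arms | Loss, MS INFoRm / control | False benefit (SD) | SE | Significant for MS INFoRm |
|---|---|---|---|---|
| 0.5 | 10% / 20% | 0.050 | 0.133 | about 6% |
| 0.3 | 15% / 34% | 0.057 | 0.124 | about 7% |
| 0.5 | 15% / 34% | 0.095 | 0.126 | about 11% |
| 0.8 | 15% / 34% | 0.152 | 0.132 | about 21% |

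Swapping the loss rates gives the same errors against MS INFoRm. In simulation (10,000 trials) with 10% and 34% lost and μ = 0.5, the false difference was 0.12 SD and 15.6% of two-sided tests rejected, whichever arm lost more.

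**3. Equal 34% loss: precision.**

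- SE with zeros (means near zero): √(2 × 0.66/100) = 0.115
- SE from the 66 per arm observed: √(2/66) = 0.174
- SE had nobody been lost: √(2/100) = 0.141

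The interval is therefore about 34% narrower than the observed data support (0.115/0.174 = 0.66), and about 19% narrower than with complete data (0.115/0.141 = 0.81). For a true difference of 0.5 SD in simulation, zero filling gave a mean estimate of 0.33 and 68.8% coverage of the nominal 95% interval; the observed scores gave 0.50 and 94.9%. Zero-filled coverage was 87.6% at 20% loss and 93.4% at 10%. With no true difference and 34% loss, type I error was 5.0 to 5.4%. Power for 0.5 SD was 80.2%, against 81.2% for completers.

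**4. Dropouts who worsen.** Suppose 34% are lost in each arm, observed MS INFoRm users improve by 0.5, lost ones worsen by 0.3, and all controls improve by 0.2.

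- Truth: 0.66 × 0.5 − 0.34 × 0.3 − 0.2 = 0.028
- Zero-filled: 0.66 × 0.5 − 0.66 × 0.2 = 0.198

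Simulated rejection was 37.9%, against 5.4% with full data. An analysis of observed scores alone did no better here: its mean was 0.30.

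**The case against.** The best defence is that the rule often does what its authors want. When loss is unrelated to outcome, equal loss alone, or an unchanged control arm alone, keeps the bias towards the null. A reader might infer that both conditions are needed; the algebra says either is enough. Nor does loss as such inflate false positives: under equal random loss the estimate and its standard error shrink together, and the t-test behaves much as it would in completers. This stands.

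The unequal-loss scenarios are also assumed. The 34% is an upper figure over time, from a pilot in which everyone received MS INFoRm, and the article plans reminders and four contact attempts. It gives no loss by arm or at 3 months. The two websites are designed to look alike, so higher loss in control is conjecture. Common improvement is not documented either. Both arms receive fatigue material, but entry requires a middle band on a different fatigue scale with the most fatigued excluded, so regression to the mean gives no clear reason to expect improvement. This stands too, and is why the milder 10% and 20% case belongs beside the larger ones.

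Finally, the proposed model rests on missing at random, which cannot be tested and fails in step 4. That is a reason to keep sensitivity analyses. It does not rescue the claim that zero change is the most conservative choice, because the direction of any imbalance in loss cannot be known in advance.

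**Conclusion.** The point holds in a limited form. The justification given for the rule is wrong in general, and zero change is a poor main intention-to-treat analysis if attrition approaches the level allowed for. Under equal random loss the harm is a diluted estimate and an interval that is too narrow, with a valid test. Under unequal loss with a common change, the harm is a false difference of μ(dC − dT): 0.05 to 0.15 SD over the tabulated cases, in favour of whichever arm loses fewer if both improve. Intervention dropouts who worsen also push the result towards MS INFoRm.

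Three stronger readings are not supported:

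- That the rule tilts the trial towards MS INFoRm. No imbalance in loss is documented and the bias can run either way.
- That the article plans an interval that is too narrow. It states tests and p-values only, so the fault lies in the standard error and in any interval reported from it.
- That this is the headline analysis. Effectiveness and efficacy are named together and neither is ranked first.

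All sizes rest on normal change scores with SD 1, 100 per arm, and assumed loss and mean change.

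**What to change.** For the effectiveness analysis of Hypotheses 1 and 2, replace zero change and last observation carried forward with a likelihood-based repeated-measures model. Fit it to all randomised participants and all observed scores at baseline, 3 months and 9 months (the visit labelled 6-month follow-up), with no single imputation, and test the group contrast at 3 months. A mixed model is already planned for Hypothesis 3, and the Sample size section says the trial was sized on one with three time points. State that last observation carried forward is not applied before the Hypothesis 3 model, which the general rule as written would allow.

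Keep zero change as a sensitivity analysis beside one that assumes dropouts did worse, because the model relies on missing at random. Delete the clause that calls the carried-forward rule the most conservative.

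The cost is revised wording and a little more analysis in the software already chosen. No new data are needed. The interval will be wider, as the observed data warrant.

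### For the single-outcome Hypothesis 3 models, the stated covariance is either redundant (unstructured plus random intercept at three visits) or reduces to compound symmetry

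*Protocol article*

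**What the plan says.** Under Statistical analysis, the Hypothesis 3 paragraph of the protocol article specifies that "a mixed-effect ANOVA will be used with an unstructured variance-covariance structure, a random intercept and terms for both a linear and quadratic trend". The same paragraph adds that "The five measures (MFIS, MSSES, PDQ, CES-D, and IPA) will be modelled simultaneously and individually". The joint analysis is tested at 0.05, and the individual analyses at 0.01, which is 0.05 divided by five tests.

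The Sample size section describes "a balanced independent-groups mixed effect model with three time points for our primary outcome". Table 2 places the assessments at months 0, 3 and 9, because the 6-month follow-up is counted from the end of the 3-month access period.

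The article does not say whether the unstructured matrix is that of the residuals or that of the random effects. It also does not say whether the trend terms are fixed or random. The general missing-data rule in the same section is last observation carried forward. The Sample size section allows for attrition "which could be as high as 34% based on our pilot study".

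**The concern.** The sentence names two devices for the same within-person correlation. With only three visits they overlap completely, or one of them loses its meaning. This affects five planned tests, because each measure gets its own model.

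The plausible readings are not equivalent. One gives the ordinary unstructured fit, with an undetermined variance split and a probable software warning. The other imposes equal variances and one common correlation on visits that are unequally spaced, which is the restriction that asking for an unstructured covariance would normally avoid. What is at stake is whether the Hypothesis 3 standard errors are right, and whether two analysts reading the sentence would fit the same model.

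**Working it through.** **Inputs from the article.** Three visits at months 0, 3 and 9 (Table 2; Sample size). Five outcomes, modelled individually and jointly. Individual level 0.05/5 = 0.01, which reproduces the stated figure. Attrition up to 34%. Correlations and variances are not given, so the correlations below are assumptions, with equal variances at all visits.

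**Step 1: count parameters for one outcome.** Three visits give 3 × 4 / 2 = 6 distinct variances and covariances. A reading is identified only if the rank of the derivative of these six elements with respect to the covariance parameters equals the number of parameters.

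| Reading | Parameters | Rank |
|---|---|---|
| Unstructured residuals + random intercept | 7 | 6 |
| Unstructured residuals only | 6 | 6 |
| Random intercept only + independent residuals (compound symmetry) | 2 | 2 |
| Unstructured matrix for random intercept and linear slope + independent residuals | 4 | 4 |
| Unstructured matrix for random intercept, linear and quadratic effects + independent residuals | 7 | 6 |

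**Step 2: what the redundancy does.** A random intercept with variance τ² adds τ² to every element of the covariance matrix, and an unstructured residual matrix can absorb that shift exactly. In one simulated data set (200 people, up to about 34% dropout, assumed correlations of about 0.5 to 0.6), τ² was set to 0, 20 and 60. All three gave the same log-likelihood (−1546.976), the same arm-by-linear estimate (−2.394, SE 0.918) and the same arm-by-quadratic estimate (0.167, SE 0.096). Only the variance split is undetermined.

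**Step 3: what compound symmetry does.** For complete data with equal variances, compound symmetry replaces the three correlations by their mean r̄. For any contrast w whose weights sum to zero, the model-based variance is proportional to (1 − r̄)Σw². The true variance is proportional to w′Rw, where R is the true correlation matrix. The SE ratio is the square root of the first over the second.

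Assume 0.7 (0–3), 0.6 (3–9) and 0.4 (0–9), so r̄ = 1.7/3 = 0.567.
- Baseline to month 9, weights (−1, 0, 1): sqrt(0.867/1.20) = 0.85.
- Month 3 to month 9, weights (0, −1, 1): sqrt(0.867/0.80) = 1.04.
- Quadratic term at 0, 3 and 9, weights proportional to (2, −3, 1). Model: 14 × 0.433 = 6.07. True: 14 + 2(−6×0.7 + 2×0.4 − 3×0.6) = 3.60. Ratio: sqrt(6.07/3.60) = 1.30.

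The real size of a nominal 1% test is 2(1 − Φ(2.576 × ratio)). This gives about 2.9%, 0.7% and 0.08% respectively. With flatter assumed correlations of 0.7, 0.7 and 0.6 the ratios are 0.91, 1.05 and 1.11.

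**Step 4: last observation carried forward.** Suppose compound symmetry were true, with all correlations 0.6 (assumed) and equal means, and all 34% left after month 3. Carrying month 3 to month 9 changes only the 3–9 correlation: 0.66 × 0.6 + 0.34 × 1 = 0.736. Then r̄ = 1.936/3 = 0.645. The SE ratio is sqrt(0.355/0.40) = 0.94 for baseline to month 9 and sqrt(0.355/0.264) = 1.16 for month 3 to month 9. The plan's own imputation rule therefore breaks compound symmetry even where the underlying data satisfy it.

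**The case against.** The strongest reply has four parts.

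- **The redundant reading does no inferential harm.** This stands. Its marginal model is plain unstructured covariance, as Step 2 shows. Removing the intercept after a warning would leave the Hypothesis 3 tests where they were.
- **The two readings are not the only ones.** This stands too. A random intercept plus random linear slope is identified, although the sentence names no random slope and that reading must treat the linear term as random and the quadratic as fixed. Natural joint five-outcome models are also identified. Of 120 distinct elements, three versions used 20, 30 and 31 parameters, each at full rank. In a joint model an unstructured 5 × 5 matrix of outcome-specific intercepts is meaningful.
- **The size rests on unseen correlations and a chosen contrast.** This stands as a limit on the figures. In the simulated data set, where the correlations were close to equal, compound symmetry gave nearly the same results: −2.410 (SE 0.937) for linear and 0.170 (SE 0.098) for quadratic.
- **A condensed article may leave such detail to the full plan.** This stands only in part. Silence on the covariance would be no finding, but the article states a covariance and a random effect, and for single outcomes that pair is defective as written.

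A reader might infer that the model cannot be fitted at all. The documents do not support that: compound symmetry can be fitted, and the redundant reading yields valid fixed-effect tests. A reader might also infer that the Hypothesis 3 tests have inflated error in general. That does not follow either, because the direction depends on the contrast, and for the quadratic term under these correlations the test is conservative.

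**Conclusion.** The concern holds for the five individual Hypothesis 3 models. As written, the covariance statement does not fix one model. Applied to the residuals, it carries seven parameters for six moments: the tests are unchanged, but the variance split is not identified and software warnings are likely. Applied to a lone random intercept with independent residuals, it gives compound symmetry, and standard errors are then wrong in a direction set by the contrast: 15% too small, 4% too large or 30% too large for the three contrasts examined.

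The parameter counts are exact. The percentages rest on assumed correlations, equal variances and complete data, and are illustrations rather than predictions for this trial. The finding does not touch the primary comparison, which is a t-test on 3-month change, and it does not show that the joint five-outcome model is unidentified.

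**What to change.** For each outcome, delete the random intercept. Fit arm, visit (months 0, 3 and 9 as categories) and arm-by-visit, with an unstructured residual covariance across the three visits (six parameters, all identified). Name the arm difference in change from baseline to month 9 as the Hypothesis 3 contrast, since the present wording leaves open which contrast represents maintenance. Linear plus quadratic terms already saturate three visits, so the categorical form has the same mean structure and nothing is lost. For the joint model, state which matrix is unstructured.

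The change costs a few lines of analysis wording, with the same data and software, provided it is made before analysis. It corrects the covariance model only; it does not remove any bias that last observation carried forward may introduce into the estimates.
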